**Methods:**

The HEPAR study (Holmium Embolization Particles for Arterial Radiotherapy) is a non-randomized, open label, safety study. We aim to include 15 to 24 patients with liver metastases of any origin, who have chemotherapy-refractory disease and who are not amenable to surgical resection. Prior to treatment, in addition to the standard technetium-99m labelled macroaggregated albumin ( ^99m^Tc-MAA) dose, a low radioactive safety dose of 60-mg ^166^Ho-PLLA-MS will be administered. Patients are treated in 4 cohorts of 3-6 patients, according to a standard dose escalation protocol (20 Gy, 40 Gy, 60 Gy, and 80 Gy, respectively). The primary objective will be to establish the maximum tolerated radiation dose of ^166^Ho-PLLA-MS. Secondary objectives are to assess tumour response, biodistribution, performance status, quality of life, and to compare the ^166^Ho-PLLA-MS safety dose and the ^99m^Tc-MAA dose distributions with respect to the ability to accurately predict microsphere distribution.

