### Treatment

#### ^166^Ho-PLLA-MS treatment dose

When the amount of lung shunting does not exceed 20% of the safety dose of ^166^HoPLLA-MS, the (complete) treatment dose of ^166^HoPLLA-MS will be administered (Figure 2). Consecutive cohorts of 3 patients will be treated with identical amounts of microspheres (600 mg), and the last cohort will consist of at least 6 patients. If no toxicity ≥ grade 3 according to the Common Terminology Criteria for Adverse Events (CTCAE)[26] is observed, the next cohort of three patients will be treated at the next radiation dose level. If in one patient CTCAE ≥ grade 3 is observed in a particular cohort, the cohort will be extended to six patients. If toxicity ≥ grade 3 is observed in two or more patients in a particular cohort, the study will be terminated because the endpoint, e.g. the maximum tolerated radiation dose, is reached. This will be reported to the Independent Ethics Committee (IEC). The dose level prior to the toxic radiation dose will become the recommended dose for efficacy studies. If an event is classified as grade 3 or 4 administration technique related, the patient will be replaced. The specific activity of the ^166^Ho-PLLA-MS will be increased by adapting the activation time in the nuclear reactor. The first, second, third and fourth cohort will be treated with a dose of 1.3, 2.5, 3.8 and 5.0 GBq/kg (liver weight), respectively. Assuming a homogenous uptake throughout the liver, this equals escalating radiation doses of 20 Gy, 40 Gy and 60 Gy, to a maximum dose of 80 Gy in the last cohort. A maximum of 15.1 GBq will be given to the maximum treated liver weight (inclusive the tumour tissue) of 3 kg (Table 2). The amount of radioactivity administered to the patient is calculated according to the following formula:

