### Follow-up

All patients are followed over a period of 12 weeks after treatment with weekly visits at the outpatient clinic. During each visit, data is collected by physical examination, WHO performance status assessment and laboratory examination (haematology, coagulation profile, serum chemistry and (if applicable) tumour marker). Adverse events are monitored. In addition, patients are asked to fill out the EORTC questionnaires in the 6 ^th ^and 12 ^th ^week post-treatment. CT and (in case of ^18^F-FDG-avid tumours) PET are performed in the 6 ^th ^and 12 ^th ^week post-treatment and MRI is performed in the 1 ^st ^and the 12 ^th ^week post-treatment (Figure 3).

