### Primary objective

The primary objective of this study is to establish the safety and toxicity profile of treatment with ^166^Ho-PLLA-MS. This profile will be established using the CTCAE v3.0 methodology and will be used to determine the maximum tolerated radiation dose. Any of the following events which are considered possibly or probably related to the administration of ^166^Ho-PLLA-MS will be considered a serious adverse event during the 12 weeks follow-up period:

• Grade 3-4 neutropenic infection (absolute neutrophil count < 1.0 × 10 ^9^/L) with fever > 38.3°C,

• Grade 4 neutropenia lasting > 7 days,

• Grade 4 thrombocytopenia (platelet count < 25.0 ×10 ^9^/L),

• Grade 3 thrombocytopenia lasting for > 7 days,

• Any other grade 3 or 4 toxicity (excluding expected AST/SGOT, ALT/SGPT elevation, elevated bilirubin and lymphopenia) possibly related to study device, using CTCAE v3.0.

• Any life threatening event possibly related to the study device: events as a consequence of inadvertent delivery of ^166^Ho-PLLA-MS into non-target organs like the lung (radiation pneumonitis), the stomach and duodenum (gastric/duodenal ulcer or perforation), the pancreas (radiation pancreatitis), and liver toxicity due to an excessive radiation dose ("radiation induced liver disease" (RILD) [10]).

The haematological and biochemical adverse events as well as RILD will be considered dose limiting toxicity.

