### Exclusion criteria

• Brain metastases or spinal cord compression, unless irradiated at least 4 weeks prior to the date of the experimental treatment, and stable without steroid treatment for at least 1 week

• Radiation therapy within the last 4 weeks before study enrolment

• Patient has received chemotherapy within 4 weeks prior to enrolment

• Major surgery within 4 weeks, or incompletely healed surgical incision before enrolment

• Any unresolved toxicity greater than National Cancer Institute (NCI), Common Terminology Criteria for Adverse Events (CTCAE version 3.0)[26] grade 2 from previous anti-cancer therapy

• Alanine aminotransferase (ALT), aspartate aminotransferase (AST), or alkaline phosphatase (ALP) >5× Upper Limit of Normal (ULN), serum bilirubin >1.5× ULN or serum creatinine >185 µmol/L

• Leukocytes <4.0 10 ^9^/l and/or platelet count <150 10 ^9^/l

• Significant cardiac event (e.g. myocardial infarction, superior vena cava (SVC) syndrome, New York Heart Association (NYHA) classification of heart disease ≥2 within 3 months before entry, or presence of cardiac disease that, in the opinion of the investigator, increases the risk of ventricular arrhythmia

• Pregnancy or breast feeding

• Comorbidity with a grave prognosis (estimated survival <3 months) and/or worse than the basic disease for which the patients will be included in the study

• Abnormalities of the bile ducts (such as stents) with an increased chance of infection

• Diseases with an increased chance of liver toxicity, such as primary biliary cirrhosis or xeroderma pigmentosum

• Patients who are declared incompetent or have a psychiatric disorder that makes a comprehensive judgement impossible, such as psychosis, hallucinations and/or depression

• Previous enrolment in the present study or previous treatment with radioembolization

• Treatment with an investigational agent within 42 days prior to enrolment

• Female patients who are not using an acceptable method of contraception or are less than 1 year postmenopausal or surgically sterile during their participation in this study (from the time the consent form is signed) to prevent pregnancy

• Male patients who are not surgically sterile or do not use an acceptable method of contraception during their participation in this study to prevent pregnancy in a partner

• Evidence of portal hypertension, splenomegaly or ascites

• Body weight >150 kg

• Active hepatitis (B and/or C)

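### The cohort rule counts any grade 3 or higher finding towards the maximum tolerated dose without reference to the patient's pre-treatment grade, and is not tied to the narrower dose-limiting list

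*Protocol article*

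**What the plan says.** **Cohort rule (Protocol article, 166Ho-PLLA-MS treatment dose).** A cohort of three with no toxicity of grade 3 or higher leads to the next dose level. For one affected patient: "If in one patient CTCAE ≥ grade 3 is observed in a particular cohort, the cohort will be extended to six patients". For two: "If toxicity ≥ grade 3 is observed in two or more patients in a particular cohort, the study will be terminated". The level below then becomes the recommended dose. Pre-treatment grade is not mentioned.

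**Event list (Primary objective).** This section says the toxicity profile will determine the maximum tolerated dose. It lists events judged possibly or probably related to the microspheres. Its item for other grade 3 or 4 toxicity leaves out expected AST, ALT and bilirubin elevation and lymphopenia. Grade 3 thrombocytopenia and grade 4 neutropenia must last more than 7 days. It ends: "The haematological and biochemical adverse events as well as RILD will be considered dose limiting toxicity". ALP is not among the items left out.

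**Entry (Appendix 1, Exclusion criteria).** Unresolved toxicity is excluded only above "grade 2 from previous anti-cancer therapy". Patients are also excluded for ALT, AST "or alkaline phosphatase (ALP) >5× Upper Limit of Normal (ULN"), so values up to that limit may enter. Bilirubin, creatinine, leukocytes and platelets have limits of their own.

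**Testing (Follow-up).** "All patients are followed over a period of 12 weeks after treatment with weekly visits at the outpatient clinic", with haematology, coagulation and serum chemistry at each visit.

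**The concern.** The trigger is an absolute grade of 3 or higher, and toxicity one grade below it is allowed at entry. The grade limit at entry covers only toxicity from earlier cancer treatment. An abnormality caused by the metastases, in a laboratory item without its own limit, may already be at the trigger grade before treatment and be found again at the first weekly visit.

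The rule stops at two patients in a cohort of three to six, so a few events of this kind can decide the trial. The maximum tolerated dose, which is the primary result, would then partly reflect who was enrolled. Because the two sections are not linked, a reader also cannot tell whether the relatedness condition and the exclusions under Primary objective apply to the cohort rule.

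**Working it through.** **1. The two definitions side by side**

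| Feature | Cohort rule | Primary objective list |
|---|---|---|
| Severity | any grade 3 or higher | listed events, grade 3 or 4 |
| Relatedness | not stated | possible or probable |
| Expected AST, ALT, bilirubin, lymphopenia | not excluded | excluded |
| More than 7 days' duration | not stated | grade 3 thrombocytopenia, grade 4 neutropenia |
| ALP | counts | counts |
| Pre-treatment grade or value | not stated | not stated |

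The columns differ in four rows. They agree in the last two, and that is where the problem remains under either reading.

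**2. The plan's own figure.** The Abstract gives the sample size: "We aim to include 15 to 24 patients with liver metastases of any origin". With four dose levels, three to six patients per cohort and at least six in the last, the minimum is 3×3 + 6 = 15 and the maximum is 4×6 = 24. Both reproduce, so the rule has been read as intended.

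**3. What a false event does.** Let p be the chance that a patient has a counted grade 3 or higher event not caused by treatment, and q = 1 − p. Assume no true toxicity and independent patients.

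- A three-patient cohort is expanded: 3pq².
- Each of the first three levels is cleared (no event in three, or one in three and none in the next three): g = q³ + 3pq²·q³.
- The last level (six patients) is cleared with at most one event: h = q⁶ + 6pq⁵.
- The study stops at some level: 1 − g³h.

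For p = 0.05: g = 0.8574 + 0.1161 = 0.9734, g³ = 0.9224, h = 0.7351 + 0.2321 = 0.9672, and 1 − 0.9224×0.9672 = 0.108.

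For p = 0.01: g = 0.9703 + 0.0285 = 0.9988, g³ = 0.9965, h = 0.9415 + 0.0571 = 0.9985, and 1 − 0.9965×0.9985 = 0.005.

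| p (assumed) | A 3-patient cohort is expanded | One 3-to-6 level stops the study | Study stops at some level |
|---|---|---|---|
| 1% | 2.9% | 0.1% | 0.5% |
| 2% | 5.8% | 0.5% | 1.9% |
| 5% | 13.5% | 2.7% | 10.8% |

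**4. What could produce p.** The documents give no baseline distribution, no visit-to-visit variation and no grade table, so this step only shows the dependence. Assume that grade 3 ALP starts above 5 times the upper limit of normal (ULN), that a patient's true level is stable, that the within-patient coefficient of variation is 10% (log-scale SD s = √ln 1.01 = 0.0998), and that the 12 weekly tests are independent. The chance of at least one value above the cut-off is 1 − [Φ(ln(cut-off/level)/s)]¹².

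- Level 3.0×ULN: z = 5.12, chance about 0.
- Level 4.0×ULN: z = 2.24, 1.3% per test, about 14% over 12 tests.
- Level 4.5×ULN: z = 1.06, 14.5% per test, about 85% over 12 tests.
- Level 4.5×ULN with a cut-off of 6×ULN: z = 2.88, 0.2% per test, about 2% over 12 tests.

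With a correlation of 0.5 between successive tests, simulation lowers the 4.0 and 4.5 figures (5×ULN cut-off) to 12% and 73%. If 10% of patients sat near the limit, a 12% chance of crossing would give p = 1.2% and a stop probability of 0.7%. A 50% chance would give p = 5% and 10.8%. If nearly all patients enter at 3×ULN or below, this source contributes almost nothing.

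**The case against.** **Primary objective governs.** It says the profile will determine the maximum tolerated dose, it names the dose-limiting events, and it asks for relatedness. An abnormality already present at screening is what attribution should remove. The monitoring committee must also review the toxicity data before each next cohort. Much of this stands. But the cohort rule does not refer to the list, and without a baseline reference the relatedness judgement in a single-arm study of patients with advancing liver disease is only a partial filter.

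**The overlap is narrow.** A reader might infer that liver enzymes in general, or all blood tests, sit at the edge of an event. The documents do not support that if the list governs: AST, ALT, bilirubin and lymphopenia are taken out when expected. For platelets, the entry limit of 150 ×10⁹/L is far from the grade 4 limit of 25 printed under Primary objective. What remains is ALP and biochemical items with no entry limit.

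**Confirmation exists.** A reader might infer that no event needs to persist. That is wrong for grade 3 thrombocytopenia and grade 4 neutropenia.

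**The numbers are assumed.** A reader might infer that a patient near the limit is almost sure to cross it, or that the trial has a one-in-three chance of a false result. Crossing is likely only very close to an assumed cut-off, under assumed variation. The one-in-three figure (34.1%) is correct arithmetic for p = 10%, but nothing in the documents points to a rate that high, and it gives attribution no effect.

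**It is a condensed article.** Baseline handling can sit in the full protocol. This would be decisive if the article were silent on the rule. It prints the full decision rule and the event list, and as printed they differ and neither uses the baseline.

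**Conclusion.** The point holds in a limited form. As printed, the rule that decides escalation, expansion, termination and the recommended dose can count an abnormality that was present before treatment, and it is not reconciled with the section that defines dose-limiting toxicity. This follows from the text and needs no assumption.

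The size cannot be fixed from the documents. For false-event rates of 1% to 5% per patient, a trial with no true toxicity stops early with probability of about 0.5% to 11%. These are illustrations that assume independent patients and that every such event is counted. The ALP figures also rest on an assumed grade 3 cut-off, variation and entry level. The change is worth making because it concerns the primary result and is cheap, not because a false result has been shown to be likely.

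**What to change.** 1. Reconcile the treatment-dose section with Primary objective, so that a single definition of dose-limiting toxicity, chosen by the sponsor, drives every step of the cohort rule.
2. Count a grade 3 or higher finding towards expansion, termination and the maximum tolerated dose only if its CTCAE grade is worse than the patient's pre-treatment grade. Word this by grade, so that it covers items that become toxic by falling (platelets, neutrophils) as well as by rising. Name the pre-treatment assessment that serves as the reference.
3. Keep reporting every absolute grade 3 or higher finding to the monitoring committee, and add a table of baseline grade against worst grade.

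This does not address a move from grade 2 to grade 3 by chance. Whether to add a minimum change or a repeat test for that case is for the sponsor to decide.

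The cost is a few sentences and one table, since screening laboratory values are already collected. The small downside is that a grade already present at baseline that persists would be reported but not counted.

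### The escalation and stopping rule counts any CTCAE grade 3 or higher toxicity, while the article's dose-limiting toxicity label covers fewer events and no rule uses it

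*Protocol article*

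**What the plan says.** In the Protocol article, the section on the ^166^Ho-PLLA-MS treatment dose sets the rule. A cohort of three with no CTCAE toxicity of grade 3 or higher leads to the next dose level. Then: "If in one patient CTCAE ≥ grade 3 is observed in a particular cohort, the cohort will be extended to six patients". And: "If toxicity ≥ grade 3 is observed in two or more patients in a particular cohort, the study will be terminated", since the MTD is taken to be reached and the level below becomes the recommended dose for efficacy studies. For 80 Gy, "the last cohort will consist of at least 6 patients". The only carve-out is: "If an event is classified as grade 3 or 4 administration technique related, the patient will be replaced".

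The Primary objective section says of the safety and toxicity profile: "This profile will be established using the CTCAE v3.0 methodology and will be used to determine the maximum tolerated radiation dose". It then lists events "considered possibly or probably related to the administration of" the microspheres, to be treated as serious adverse events over the 12 weeks of follow-up. Within that list:

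- expected AST and ALT elevation, elevated bilirubin and lymphopenia are excluded from the general grade 3-4 item;
- grade 4 neutropenia counts only beyond 7 days, and so does the lesser platelet toxicity ("Grade 3 thrombocytopenia lasting for > 7 days").

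The section closes by naming the haematological and biochemical events, together with radiation-induced liver disease (RILD), as dose limiting toxicity. No escalation, expansion or stopping rule refers to that label.

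**The concern.** In a dose-escalation trial, the event counted by the escalation rule should be the event that defines the MTD. Here the rule counts one set of events, and the section that sets the primary objective labels a narrower set as dose limiting. The sets differ most clearly on two kinds of event: the laboratory changes that the list excludes as expected, and cytopenias that resolve within 7 days. Both can be device-related and of grade 3 or higher.

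The MTD is the trial's main output and fixes the dose carried into efficacy studies. The plan also looks closely for such events. Follow-up runs for 12 weeks "with weekly visits at the outpatient clinic", each with haematology and serum chemistry. Under Appendix 1, patients may enter with AST or ALT up to 5 times the upper limit of normal, and with unresolved grade 2 toxicity from earlier therapy. The stopping rule makes no allowance for baseline.

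**Working it through.** **Design figure.** The stated sample size reproduces: at least 3 + 3 + 3 + 6 = 15 patients and at most 4 × 6 = 24. It does not depend on how the event is defined.

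**The two texts side by side.**

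| Event, device-related | Stopping rule | Primary objective section |
|---|---|---|
| Expected AST/ALT elevation, grade 3 | Counts | Excluded from the list |
| Grade 3 thrombocytopenia, 7 days or less | Counts | Below the duration limit |
| Grade 4 neutropenia without infection, 7 days or less | Counts | Below the duration limit |
| Post-embolization symptoms, grade 3-4 | Count | On the list, but not in the dose-limiting sentence |
| RILD | Counts | Dose limiting |

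The general grade 3-4 item cannot be meant to bring short cytopenias back in, because the 7-day limits would then do nothing.

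**Worked case.** Two of three patients at 40 Gy have an expected, device-related grade 3 transaminase elevation. The stopping rule ends the study and 20 Gy becomes the recommended dose. Under the dose-limiting label, none of these events counts.

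**Size.** The article gives no event rates, so the following are assumptions. Let b be the share of patients whose only grade 3 or higher events are ones that the Primary objective list leaves out. Take b as constant over dose levels, with no true DLT and exactly six patients at 80 Gy. With p the chance that a patient counts under the rule (here p = b):

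- Clear a level: c = (1 − p)^3 + 3p(1 − p)^5, that is 0 of 3, or 1 of 3 followed by 0 of 3.
- 80 Gy tolerated: t = (1 − p)^6 + 6p(1 − p)^5, that is at most 1 of 6.
- Stop before 80 Gy: 1 − c^3.
- Recommended dose below 80 Gy: 1 − c^3 × t.

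For b = 5%, c = 0.8574 + 0.1161 = 0.9734 and t = 0.7351 + 0.2321 = 0.9672. Then 1 − c^3 = 0.078 and 1 − c^3 × t = 0.108.

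| b | c | t | Stop before 80 Gy | Recommended dose below 80 Gy |
|---|---|---|---|---|
| 2% | 0.9954 | 0.994 | 1.4% | 1.9% |
| 5% | 0.9734 | 0.967 | 7.8% | 10.8% |
| 10% | 0.9061 | 0.886 | 25.6% | 34.1% |

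If b instead rises with dose (0% at 20 and 40 Gy, 5% at 60 Gy, 10% at 80 Gy), the two probabilities are 1 − 0.9734 = 2.7% and 1 − 0.9734 × 0.886 = 13.8%.

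**With some true DLT.** Let the true DLT rate be d = 5%, independent of b, so that p = 1 − (1 − d)(1 − b). Counting true DLT alone, the recommended dose falls below 80 Gy in 10.8% of trials. Adding b = 2%, 5% or 10% gives p = 0.069, 0.0975 or 0.145, and the probability rises to 18.9%, 32.8% or 55.9%.

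**The case against.** The strongest reply is that the exclusions and duration limits belong to a list of serious adverse events, not to a definition of the MTD. The sentence that ties the MTD to the toxicity profile mentions only CTCAE methodology, which fits the stopping rule. That is correct as far as it goes. A reader might infer that the article expressly bases the MTD on the restricted list, and it does not. The link is the natural reading of the MTD sentence before the list and the dose-limiting sentence after it. What remains is that a dose-limiting label exists, is narrower than the stopping rule and drives nothing.

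The word toxicity may also imply attribution to the device. Granting this does not remove the mismatch, because an expected transaminase rise or a short cytopenia can be device-related.

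Counting all grade 3 or higher toxicity is a defensible, cautious choice in a first-in-human trial. That stands, but the label should then agree with it.

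The Independent Data Monitoring Committee (IDMC) sees all grade 3 or higher toxicity and must permit each next cohort. The article gives it no event definition, and its permission does not override a rule that says the study will be terminated.

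The dose-limiting sentence may omit pneumonitis, ulcer or perforation, and pancreatitis on purpose, because the article describes them as results of misdirected delivery, for which patients are replaced. That is a coherent reading. Replacement, however, requires a technique-related classification and covers grades 3 and 4 only.

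Finally, entry limits on platelets, leukocytes and bilirubin screen out some patients nearest to toxicity, so the baseline argument holds mainly for transaminases. Weekly testing helps detection and says nothing about frequency.

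**Conclusion.** The point holds as a mismatch between two definitions printed in the article, so it is not a detail left to another document. It should be fixed. The firm part is textual: events left out of the dose-limiting label can end the trial and set the recommended dose.

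The size is conditional. It rests on assumed rates, independence between patients and exactly six patients at 80 Gy. At 2% with no true DLT the effect is small (about 2% of trials). At 5% and 10% it is about 11% and 34%. Nothing in the article favours one of these rates.

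A reader might also infer two further things that the article does not support. One is that patients are put at risk: the literal rule errs towards a lower dose. The other is that post-embolization symptoms show the same conflict. The Safety profile section says that they may reach grade 3 or 4 without direct clinical relevance, but related symptoms of that grade are on the Primary objective list and fall outside only its dose-limiting sentence.

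**What to change.** Define DLT once and write the three limbs of the rule (0 of 3, 1 of 3, two or more) in its terms. A workable definition:

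- the events on the Primary objective list, possibly or probably related to the microspheres and occurring within 12 weeks, with that list's laboratory exclusions and duration limits;
- including RILD, related deaths and life-threatening events from non-target delivery;
- except grade 3-4 events classified as technique related, where the patient is replaced as now.

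The dose-limiting sentence should not simply be adopted as it stands, since read literally it omits pneumonitis, ulcer or perforation, and pancreatitis. State whether self-limiting post-embolization symptoms count, and how worsening from a raised baseline is graded. Use the same definition in the IDMC review (Statistical considerations and Monitoring), and keep reporting all grade 3 or higher toxicity to the committee.

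The cost is protocol wording, with no extra patients or data. The downside is a somewhat less conservative stopping rule, mitigated by the IDMC's permission before each next cohort. The cautious alternative is to keep the stopping rule and delete the exclusions, duration limits and dose-limiting label. That is consistent too, but it accepts the early stops shown above.
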